## Background

Antiretroviral therapy (ART) scale-up in sub-Saharan Africa (SSA) has been rapid with an estimated 16.4 million individuals on ART by the end of 2018 [1]. The increased expansion in the indication for ART use would result in earlier initiation of treatment and if adherence is suboptimal, could lead to virological failure and the likely development of drug resistance. The likelihood of transmission of resistant virus will depend on ART coverage, duration of ART roll-out and the proportion and absolute numbers of individuals with virological failure [2–4]. Conditions that would influence transmission of resistant virus include proportion of failures with resistant virus, time spent on failing regimen, viral load (VL) of patients with resistant virus, fitness of the resistant virus and the transmission probability compared with ART-naïve individuals [2]. The availability of viral load monitoring (VLM) in resource-rich countries, means individual failing treatment are identified early and switched to alternative suppressive ART. In contrast, many sub-Saharan African countries rely on World Health Organisation (WHO) immunological and clinical criteria for identifying treatment failure which has poor sensitivity and specificity [5]. In settings where there is availability of VLM, their effectiveness has been hampered by poor adherence to monitoring guidelines by healthcare providers [6].

South Africa has the biggest HIV treatment programme in the world with 7.7 million individuals living with HIV and 62% currently receiving ART within a stretched health system [1]. VLM has been part of the public ART programme since roll-out in 2004 and requires people living with HIV (PLHIV) initiating ART to have a VL measured at 6 months and 12 months after ART initiation and 12-monthly thereafter if virologically suppressed [7, 8]. Those with a VL ≥ 1000 HIV-1 RNA copies/mL should be retested after 3 months of adherence counselling support, and then either retained on first-line therapy if re-suppressed or switched to second-line therapy if VL ≥ 1000 copies/mL [7].

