#### Augmentation of TIER.Net with a dashboard system

TIER.Net is an electronic database with varying levels of sophistication in both functionality and reports. It ranges from an off-line version of the electronic register to hybrid that is predominantly offline, with synchronisation centrally when bandwidth allows to a networked electronic version of the paper register [9]. The offline version of TIER.Net is in operation in the public ART programmes in which this study will be embedded.

As part of the proposed intervention, VL results will be imported into TIER.Net daily from the National Health Laboratory Service (NHLS) which will be linked to patients in TIER.Net based on multiple exclusive and linked deterministic rules using a combination of variables such as name, surname, sex, date of birth, date of visit, NHLS lab number, facility and folder number. The information contained in TIER.Net will be used to develop a dashboard which will display the following information:The proportion due VL tests as per South African ART guidelines.The proportion with high VLs (VL ≥ 50 copies/mL).The proportion lost to follow-up.Those with confirmed virological failure (repeat VL ≥ 1000 copies/mL after a first VL 1000 copies/mL measured ≥ 3 months apart).

A dashboard has the advantage of displaying a quick visual state of affairs and how this evolves with time. This will incorporate a text messaging functionality that can be used by healthcare workers/viral load champion to communicate with patients.

It is envisaged that these interventions will result in prompt identification of patients who require VLM, and improve clinical management of virological failure thereby improving the quality and efficiency of service delivery.

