##### Secondary outcomes

Proportion of all patients with at least one documented VL in TIER.Net during the trial follow up.Proportion with VL ≥ 50 copies/mL during follow upProportion with VL ≥ 1000 copies/mL during follow up (virological failure)Among patients with VL ≥ 1000:Proportion with a repeat test within 3 monthsTime from first VL ≥ 1000 copies/mL to repeat VL.Proportion switching to second-line ART after two consecutive VL ≥ 1000 copies/mL measured ≤ 3 months apartProportion completing the treatment failure cascade (VL < 50 copies/mL on repeat testing or switch to second line ART)Cost-effectiveness of the intervention compared to current care with respect to the primary outcome (viral suppression at 12 month follow-up) and two secondary outcomes (proportions of patients with VL ≥ 50 copies/mL and VL ≥ 1000 copies/mL)Acceptability, fidelity, adaptation and contexts in the implementation of the interventions

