#### Evaluation of the intervention impact

TIER.Net has information on HIV-positive individuals on ART including unique South African Identification number, age, sex, date of ART initiation, viral load results and dates, CD4 count results and dates, type of ART regimen, status of the individual (whether still in care, lost to follow up or dead), and dates of clinic appointments. The clinical charts of the 150 participants per clinic who are in the evaluation cohort will be reviewed to extract these baseline data for entry into REDCap. These will be repeated after each participant has completed 12 months of follow up in their clinic/cluster to capture documentation of VL being measured, test data and the results of the VL. These data will be used to evaluate the impact of the intervention on VLM and virological suppression, and on the treatment failure cascade. Data on all clinic visits irrespective of reason for the visit will be extracted from ClinicLink. These will be used to describe patterns of health care use among the trial population. HIV-positive individuals receiving care in the clinics are not the recipients of the quality improvement interventions, which will be focussed on the nurses and systems for delivering care. Hence, interim visits for any intercurrent illness by patients will be managed as per standard clinical care and will not be routinely reported as adverse events.

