### Research ethics and consent

This study is registered with Clinicaltrials.gov (NCT05071573). The main study findings will be reported in accordance the Consolidated Standards of Reporting Trials (CONSORT) statement [20]. The study protocol v1.1, 19 Aug 2020 received ethical approval from the Biomedical Research Ethics Committee of the University of KwaZulu-Natal (BREC/1531/2020), the Research Governance and Ethics Committee of the Brighton and Sussex Medical School (ER/BSMS9B5G/4) and the KwaZulu-Natal Health Research Committee (KZ_202008_092). Any protocol amendments will need to be approved by all regulatory authorities mentioned above prior to implementation. Research staff will be trained in the amended protocol and any updated study materials and consent forms will be administered to the relevant participants as necessary. The University of Sussex is the sponsor of the study.

The operational managers of the 10 trial clinics will be given clear explanations about the trial aims, and the nature, scope, and possible consequences of their facilities and staff participating in the research by the study coordinator. Managers will be asked to provide written informed consent for their facilities to participate in the trial and be randomised to one of the two trial arms, and for review of clinical records of patients.

The principal investigator and study coordinator will schedule meetings with nursing staff from the 10 clinics, to explain the intervention and the trial aims. Nurses will be asked to consent to participation in the trial, and to receive further training as viral load champions if selected. They will be offered consent for participation in the process evaluation (not described in this protocol).

The informed consent process will be administered by a research assistant through REDCap with electronic signature obtained from nurses participating in the QIP. The nurses will be given paper copies of the participant information leaflets and consent forms.

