The observed poor VLM in KwaZulu-Natal could be due to a number of reasons; patients may not have been aware of or empowered to request recommended blood tests, facility staff may be inadequately trained, or have insufficient time or resources to conduct blood tests when due, failure of results to reach clinics from the laboratory or failure to capture results on TIER.Net as these are manually entered [10]. The current study proposes to investigate the clinical and process impediments in VLM, including a review of patients’ clinical charts and comparing viral load in the charts with viral load data manually captured on TIER.Net in order to clarify whether the reported poor VLM was due to poor data entry in TIER.Net or actual failure to monitor viral loads. The proposed interventions will address all the steps potentially implicated in the poor management of VLM. This will involve training of staff on the current South African ART guidelines [26], designating a viral load champion who has administrative responsibility for identifying individuals due viral load tests or those with confirmed virological failure who need to be switched to second-line ART [17]. The automatic import of viral load results from the NHLS laboratories, also eliminates staffing challenges which contributes to backlogs in data capture and data entry errors. We also observed that amongst those with VLM who are experiencing virological failure, there is poor health system response to the clinical management of this situation. Only a minority of those with elevated viral load had a repeat viral load to confirm virological failure on ART, with only a small proportion of those with confirmed virological failure switching to second-line ART [10].

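### The second-line switch outcome requires the two high viral loads to be at most 3 months apart, but the protocol defines confirmed failure by a gap of at least 3 months

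*Protocol article*

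**What the plan says.** Four parts of the protocol article bear on this point.

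- **Outcome measures, Secondary outcomes.** Among patients with a viral load of 1000 copies/mL or more, one outcome is the proportion switching to second-line ART "after two consecutive VL ≥ 1000 copies/mL measured ≤ 3 months" apart. The same list has two outcomes on retest timing (a repeat test within 3 months, and time to the repeat test). It also has completion of the "treatment failure cascade (VL < 50 copies/mL on repeat testing or switch to second line ART").
- **Augmentation of TIER.Net with a dashboard system.** The dashboard is to show patients with confirmed virological failure, defined as a "repeat VL ≥ 1000 copies/mL after a first VL 1000 copies/mL measured ≥ 3 months apart".
- **Background.** Under the care rule, patients at or above 1000 copies/mL "should be retested after 3 months of adherence counselling support". They are then switched if the result is still at or above that level.
- **Discussion.** The viral load champion is to identify "those with confirmed virological failure who need to be switched to second-line ART". The earlier work is reported as finding few patients retested, "with only a small proportion of those with confirmed virological failure switching to second-line ART".

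**The concern.** The inequality in the switch outcome points the opposite way from the one in the definition of confirmed failure, and nothing in the protocol reconciles them. The intervention brings forward patients whose two high results are at least 3 months apart. The outcome that should show whether they were switched accepts only pairs at most 3 months apart.

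At stake is what this outcome means. A clinic that follows the care rule, retests a little after 3 months, finds continuing failure and switches the patient gets no credit for it here. A clinic that retests early and switches does. The reported figure would not answer the question the Discussion raises, namely how many confirmed failures are switched.

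**Working it through.** The protocol states no figure on this point that could be reproduced. The check compares definitions and then applies them to two constructed patients.

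**Step 1: the conditions side by side.** Let *t* be the time between the two results of 1000 copies/mL or more.

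- Switch outcome (Secondary outcomes): *t* ≤ 3 months.
- Confirmed virological failure (dashboard section): *t* ≥ 3 months.
- Care rule (Background): retest once 3 months of counselling have passed, which fits *t* ≥ 3 months.

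The first two conditions are both satisfied only at *t* = 3 months exactly. The Discussion gives no interval of its own, but it ties the need to switch to confirmed failure, and the dashboard section holds the protocol's only definition of that term. The switch outcome is the one that does not fit.

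**Step 2: two example patients.** The protocol does not convert months to days. I assume 3 months = 91 days, with a range from 3 × 28 = 84 to 3 × 31 = 93.

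- Patient A: results of 1000 or more on days 0 and 98, switch on day 112. Gap: 98 − 0 = 98 days.
- Patient B: results of 1000 or more on days 0 and 70, switch on day 84. Gap: 70 − 0 = 70 days.

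| Condition | A (98 days) | B (70 days) |
|---|---|---|
| Switch outcome as written, gap ≤ 84 / 91 / 93 | no / no / no | yes / yes / yes |
| Confirmed failure, gap ≥ 84 / 91 / 93 | yes / yes / yes | no / no / no |
| Switch outcome with the sign reversed, gap ≥ 84 / 91 / 93 | yes / yes / yes | no / no / no |
| Cascade completed by switching | yes (day 112) | yes (day 84) |

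The classification is the same at all three day counts, so the month convention does not drive it.

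**Step 3: how many patients.** The share of confirmed failures that the outcome misses equals the share whose gap exceeds 3 months. The protocol gives no distribution of retest times. The Background reports a median of one year from failure to change of therapy, which is time to switch and not time to retest. The missed share could be 0% (every confirming sample taken at exactly 3 months) or close to 100% (nearly all taken later). For the same reason, the direction of any effect on the comparison between arms cannot be derived.

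**The case against.** The best defence is that the short interval is deliberate. The outcome list already includes a repeat test within 3 months, so the items can be read as a prompt-care sequence: retest within 3 months, then switch on that result. Prompt management is a stated aim. The definition with the longer interval sits in the description of the intervention, is itself missing an inequality sign before the first 1000, and the outcome list does not use the term confirmed failure. These facts are correct, and they leave some doubt about what was intended. They do not rescue the text. Promptness already has two outcomes of its own, nothing says that the switch outcome rests on a different concept of failure, and under the prompt-care reading it would still leave out patients retested after the counselling period that the care rule prescribes.

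Three objections to reversing the sign have some force:

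- A patient whose repeat test falls within 3 months and is high would succeed on the repeat-test outcome, yet that pair could not qualify for the switch outcome except at exactly 3 months. This is true, and it is Patient B's case. It is the price of measuring switching among confirmed failures.
- The word requiring consecutive results, which is already in the outcome, can work against frequent testing. With high results on days 0, 60 and 120, the consecutive gaps are 60 and 60 days, so the reversed condition fails, although days 0 and 120 are 120 days apart. This is an edge case for the derivation rules to settle.
- No upper limit is set on the gap. Late retests up to the end of follow-up would qualify.

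It is also fair to say that the consequence is limited and its size unknown, and that a detailed analysis plan is promised before analysis. But the protocol states this interval explicitly, so a plan that copies it carries the problem forward.

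**Conclusion.** The concern holds. The switch outcome as written uses the reverse of the protocol's own interval for confirmed virological failure and conflicts with the care rule. It excludes patients managed by that rule whose retest falls after 3 months, and it admits patients who are not confirmed failures. The scoring of individual patients is certain for 3 months taken as 84 to 93 days. The number affected and the effect on the between-arm comparison are not derivable.

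The scope is one secondary outcome. The cascade outcome has no interval condition and counts every switch, time to repeat test keeps the later retests, and a repeat test within 3 months can stand as a timeliness measure. The primary outcome, the sample size and the primary analysis are untouched. It should be corrected, but it does not threaten the trial's main result.

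**What to change.** Before analysis, redefine the switch outcome as switching after two consecutive results of 1000 copies/mL or more that are at least 3 months apart, and derive it from dated results in the same way in both arms. In the derivation rules, fix the number of days taken as 3 months and say how a high result falling between the two qualifying ones is handled.

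State the downside openly: patients switched after two high results less than 3 months apart no longer meet the interval condition, though the cascade outcome still counts them. Late retests will qualify, and the time-to-repeat outcome will show how late they were.

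The cost is one inequality sign, its derivation code and those two rules. No new data are needed, since the section Evaluation of the intervention impact lists "viral load results and dates" among the data held. If the change is treated as an amendment, Research ethics and consent applies: "Any protocol amendments will need to be approved by all regulatory authorities mentioned above prior to implementation". That means the three ethics and research committees named there.

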### Sample size justification

#### Health system gaps

The precision with which the prevalence of each outcome can be estimated will depends on the prevalence itself and the amount of correlation within clinics (the ‘design effect’). For a prevalence of 30%, a sample size of 800 patients will allow us to estimate it with a precision of ± 4.5 or ± 5.5% with 95% confidence if the design effect is 2 or 3, respectively. For a prevalence of 60%, the corresponding figures are ± 4.8 and ± 5.9%. This sample size will also allow us to determine the association of factors with a missing VL measurement. For example, if the design effect is 2, assuming the prevalence of missing VL is between 30 and 60%, we would have > 80% power to detect an OR of 2.25 or more for factors associated with missing VL, if the prevalence of the risk factor among those with non-missing VL is between 15 and 70%. This would allow us to identify any strong predictors of missing VL.

#### Evaluation of the intervention

We estimate that during the 3 month recruitment phase, an average of 150 patients who have been on ART for ≥ 12 months will attend each clinic. Based on our previous work, we expect that around 50% of patients in the control arm will have a VL measurement and be virally suppressed at the end of follow-up. With 5 clinics per arm, assuming a coefficient of variation, k, of 0.20, and a sample size of 150 patients per clinic, we would have 80% power to detect an increase in the proportion of patients who have a VL measurement and are virally suppressed from 50% in the control arm to 77% in the intervention arm (Table 1).

**Table 1 Tab1:** Numbers needed to demonstrate an improvement in viral load monitoring, for different assumptions regarding clinic size and effect sizes

Number of clinics per arm	Number of patients per clinic^1^	Coefficient of variation (k)	% with VL suppressed in control	% with VL suppressed in intervention	Power (%)
5	100	0.20	45	67	71
5	100	0.20	45	70	80
5	100	0.20	50	74	71
5	100	0.20	50	77	80
5	100	0.20	55	80	70
5	100	0.20	55	84	80
5	150	0.20	45	66	70
5	150	0.20	45	69	80
5	150	0.20	50	73	70
5	150	0.20	50	77	80
5	150	0.20	55	80	70
5	150	0.20	55	84	80

^1^Harmonic mean to account for varying facility size

### Recruitment

#### Health system gaps

We will create sampling frame of all HIV-positive patients who are in care at the ten trial clinics and who started ART in the previous 15–18 months. We will select a random sample of 800 individuals above the age of 16 years from this list. The clinical notes of these individuals will be reviewed to identify any gaps in the viral load monitoring process.

#### Evaluation of the intervention

The effectiveness of the intervention will be evaluated in HIV-positive individuals aged ≥ 16 years attending the trial clinics who have been on ART for at least 12 months at baseline (the evaluation cohort).

AHRI has a clinical research assistant stationed in each of the ten clinics who registers every patient attending the clinic, irrespective of their reason for attendance or HIV status. A database, known as ClinicLink, was developed in-house at AHRI for the registration of clinic visits and reasons for attendance. ClinicLink will be used to identify patients attending the clinic who meet the criteria for inclusion in the evaluation cohort. Based on current clinic attendance, we will need about three months to meet the target sample size of an average of 150 patients per clinic. These individuals will form the basis for the main analyses. In secondary analyses, all patients meeting these criteria who attend one of the trial clinics during the three-month recruitment phase will be included in the evaluation cohort, even if the sample size is exceeded since the target sample size is considered a minimum. If the target sample size is not met within 3 months, we will extend the recruitment phase for another month as necessary.

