## Methods

### Trial setting

The trial will be hosted by the Africa Health Research Institute (AHRI), an independent scientific research institute and a Wellcome Trust Africa and Asia Programme. AHRI has two campuses 250 km apart; the Population Intervention Programme (PIP) study area in uMkhanyakude district in northern KZN with a population of 625,846, and a state-of-the-art laboratory infrastructure in the city of Durban.

The PIP is an extensive social, demographic, HIV and clinical research programme of an under-resourced rural population of 140,000 in an area of about 845 km^2^. Hlabisa is at the epicentre of the HIV epidemic in South Africa, where HIV prevalence among men and women aged 15–54 years in 2018 was 19% and 40% respectively [16]. It is situated in the most economically deprived district nationally; about 5% of adults have completed a higher education, 4% are covered by a medical aid scheme and unemployment rate is 62% [16]. AHRI has a memorandum of understanding with the DoH to support HIV care in the Hlabisa sub-district with ~ 30,000 PLHIV currently on ART (still in active care) in the 17 primary healthcare clinics (PHC) in the catchment area. This trial will be implemented in 10 of the 11 primary health care clinics that are located within the catchment area of the PIP.

The study involves collaboration of investigators from AHRI, the University of Sussex (UoS) and the University of Cape Town (UCT).

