### Description of the intervention

#### Quality improvement package

We will adapt the VL champion model described by Sunpath et al. [17]. This model identifies a VL champion in each clinic who dedicates 10 h per week to the role. The VL champion ensures those with high VL are appropriately managed with repeat VL tests including referral to a doctor for second line ART switch if required.

The prototype QIP will be adapted based on the identified clinical and process impediments in VLM from the gap analysis. All nursing/assistant staff in the intervention clinics will be trained on the QIP using the model by Sunpath et al. as described above [17]. Each intervention clinic will identify two key nurses who would act as VL champions. Their role will include tracing and recalling patients who need further assessments of their VL or switch to second-line regimen.

Training will be provided in the use of enhanced TIER.Net technology that will be developed as part of the trial and how to access reports on the dashboard system.

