### Trial procedures and timelines

We will pilot the interventions over 3 months to address any issues raised and deliver further training to the nurses or adaptation of the technology if required (Fig. 2). Patients attending for their routine clinic visits over a three month period, which we estimate is the time required for at least 150 participants to pass through each clinic, will be included in the evaluation cohort and followed up for a period of 14 months to allow a 2 month window for appointment reschedules etc.

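### Cohort entry is by clinic attendance, apparently after the intervention has begun, and only intervention clinics recall patients, so membership can depend on arm

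*Protocol article*

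**What the plan says.** All references are to the Protocol article.

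- **Entry.** Participants defines the cohort as patients aged 16 or over, on ART for at least 12 months, who attend a trial clinic in a three-month recruitment period. Recruitment (Evaluation of the intervention) adds: "ClinicLink will be used to identify patients attending the clinic who meet the criteria for inclusion in the evaluation cohort". Every attender is registered, whatever the reason for the visit. The target of about 150 per clinic forms the main analysis; all eligible attenders form a secondary one.
- **Timing.** Trial procedures and timelines opens with "We will pilot the interventions over 3 months to address any issues raised", mentions further nurse training, and then describes the recruitment window. There the visits that count are routine ones.
- **Intervention.** Quality improvement package trains the staff of the intervention clinics and appoints two champions in each: "Their role will include tracing and recalling patients who need further assessments of their VL or switch to second-line regimen". The dashboard section adds text messaging to patients. Standard of care describes neither.
- **Blinding.** Research staff and nurses know the allocation.
- **Expected numbers.** "we will need about three months to meet the target sample size of an average of 150 patients per clinic".

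**The concern.** Randomising clinics protects the comparison if the patients counted in each clinic are identified independently of allocation. Here entry requires a visit, and in one arm part of the package exists to generate visits. Patients are recalled because of their VL status, which underlies the primary outcome (VL measured and suppressed). If the package is running when the window opens, the intervention cohort can include people whose counterparts in control clinics do not attend and are never counted. This is identification bias after randomisation, and its effect would be mixed into the estimated effect of the intervention.

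A second issue is that the two descriptions of entry differ. Recruitment takes patients attending the clinic; the timelines section takes patients at routine visits. Whether a recall visit admits a patient depends on which is followed.

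**Working it through.** **1. Sequence.** The pilot is described before the recruitment window. It includes further training of nurses, and the nurses trained on the package are those of the intervention clinics. A pilot of that kind implies that allocation is already known. No sentence says so: randomisation is not dated, the pilot clinics are not named, and the baseline period in Participants has no dates.

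**2. The plan's own power figure.** Inputs: "With 5 clinics per arm, assuming a coefficient of variation, k, of 0.20, and a sample size of 150 patients per clinic"; "from 50% in the control arm to 77% in the intervention arm"; "we would have 80% power to detect an increase". Two-sided 5% significance is assumed, in line with the planned 95% interval. For an unmatched cluster trial (Hayes–Bennett):

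power = Φ( √[ (c−1)(p1−p0)² / V ] − 1.96 ), with V = p0(1−p0)/m + p1(1−p1)/m + k²(p0²+p1²).

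With c = 5, m = 150, k = 0.20, p0 = 0.50, p1 = 0.77:
- V = 0.00167 + 0.00118 + 0.03372 = 0.03656
- (c−1)(p1−p0)² = 4 × 0.0729 = 0.2916
- √(0.2916/0.03656) = 2.824, and Φ(0.864) = 80.6%.

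The stated 80% reproduces, as do all 12 rows of Table 1 (largest gap 1.3 points). The sample size is not in question.

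**3. What selective entry could do (illustration).** Let s be the share of the intervention cohort present only because of recall, and p_r their success probability. Neither is in the document. With no true effect, the expected risk ratio is [0.50(1−s) + p_r·s]/0.50:

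| s (assumed) | p_r = 0.20 | p_r = 0.80 |
|---|---|---|
| 5% | 0.97 | 1.03 |
| 10% | 0.94 | 1.06 |
| 20% | 0.88 | 1.12 |
| 30% | 0.82 | 1.18 |

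For s = 20%, p_r = 0.20: (0.40 + 0.04)/0.50 = 0.88. The two-sided type I error is then about 13%; with p_r = 0.80 it is about 11%. Both use a t-test on clinic proportions with 8 df, as an approximation to the planned stratified test on logs.

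If the true effect is 50% vs 77% and recalled patients succeed at 0.50, the intervention proportion becomes 0.77(1−s) + 0.50s. At s = 20% that is 0.716, and the formula in step 2 gives 65.5% power. At 10% and 30% it gives 73.8% and 56.0%.

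**4. A separate check on the 150.** Trial setting reports about "30,000 PLHIV currently on ART (still in active care) in the 17 primary healthcare clinics". 30,000/17 ≈ 1,765 per clinic, and 150/1,765 = 8.5%. At one visit a year (assumed), 1,765/4 ≈ 441 would attend in three months; if half were eligible (assumed), about 220.

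**The case against.** Several objections carry weight.

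- **Routine visits only.** If the timelines wording governs and is enforced, recall visits do not admit anyone, and ClinicLink records reasons for attendance, so the rule could be applied. This stands as a mitigation. However, neither Participants nor Recruitment carries that limit.
- **Uniform registration.** Every attender is registered in all ten clinics. This rules out selective registration by unblinded staff but leaves differential attendance.
- **Baseline data.** A reader might infer that the bias could be neither detected nor repaired. That is too strong. The charts and TIER.Net hold dated VL and CD4 results, so records from before allocation can be compared and adjusted for. The adjusted analysis is optional as planned, however, and baseline values taken at recall visits may already reflect the package.
- **Size.** The values of s are assumptions. At 20%, 30 of an intervention clinic's 150 patients would have to be there only because of recall. The adapted model gives the champion role 10 hours a week, and patients who would have attended anyway do not change membership. If most patients visit within any three months, the effect could be small, especially in the analysis of all attenders.
- **Clinic average.** A reader might take 1,765 per clinic as proof that the 150 would fill within days with early and recalled attenders. It is not. The average covers 17 clinics, while the trial uses ten, and it includes patients who are too young or too recently on ART. Recruitment does not say that places fill consecutively. What remains is a query about the estimate.

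**Conclusion.** The concern holds in a limited form. Entry by attendance, in a window that appears to follow the start of the interventions and with recall and texting in one arm only, means that cohort membership can depend on arm. A reader might infer that it does depend on arm, or that recruitment is stated to follow randomisation. The article supports neither: the order of events is a reasonable inference from the timelines section and from who is trained.

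Size and direction are unknown. Recalled patients with high or overdue VL would lower apparent success in the intervention arm; re-engaged patients could raise it. At an assumed 5–30% recalled share and success probability of 0.20–0.80, the null risk ratio spans 0.82 to 1.18. This range shows sensitivity and does not predict what will happen. The disagreement over which visits count is in the text and does not rest on any assumption. The change is worth making because it is cheap and removes the question; the power calculation is unaffected.

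**What to change.** 1. Define the eligible list for every clinic, in both arms, from TIER.Net/ClinicLink at a cut-off date before allocation, or at the latest before the pilot starts. Alternatively, count only visits already scheduled before that date. If allocation has taken place, the same cut-off can be applied retrospectively to existing visit records.
2. Draw a random 150 per clinic from the list for the main analysis and use the whole list for the secondary analysis. The gap analysis already samples at random from a list.
3. Take baseline VL and covariates from records dated before the cut-off.
4. Reconcile Recruitment with Trial procedures and timelines on which visits count, and date randomisation, pilot and recruitment in the text.
5. Report eligible numbers and reason for attendance by arm.
6. Separately, check the estimate of 150 in three months against ClinicLink counts.

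**Cost.** Protocol wording and a data query; the data are routine and patient consent is waived, so no extra contact is needed. The start of each participant's 12 months must be restated. Some listed patients will leave care before follow-up starts and stay in the denominator, which dilutes the effect slightly. For example, if 5% in each arm leave and count as failures (assumed), a 27-point difference becomes 27 × 0.95 = 25.65 points, with the risk ratio unchanged.
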